### Design and setting

This multicenter study has an open-label, randomized, parallel-group design. Patients will be randomized 1:1 to SCS using the Specify® 5-6-5 surgical lead (Medtronic, Inc.) plus OMM (SCS group) or to OMM alone (OMM group) and followed for 6 months (Period I, randomized comparative phase). After completion of the 6-month (Period I) outcome assessment, patients will be systematically reminded (through electronic tablets used for questionnaire completion) that they have completed the randomized period of the study and can change treatment to that received by the other randomized group. Reasons for treatment switching will be recorded. Patients will be followed to 24 months post randomization (Period II, long-term observational follow-up phase).

The trial will be conducted at approximately 30 investigative sites globally, with approximately 15 to 20 sites in the USA and 10 to 15 sites in Europe and Canada. Additional locations may be added during the course of the study. No single center can exceed 10% of all randomized patients. The study design is summarized in Figure 1.

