### Assessments

Outcome measures selected for this trial are based on a review of the previous RCTs of SCS and a consideration of IMMPACT recommendations [18].

The day of randomization is day 0 for the study periods. Subjects will be assessed prior to randomization (baseline) and at 1-month, 3-month, 6-month, 9-month, 12-month, 18-month and 24-month follow-up visits. Visit windows for Period I and Period II will remain constant based on the original date from the randomization visit, regardless of whether any change in therapy occurs. Assessments will be performed by appropriately trained and delegated study staff according to the usual practices of the site. Electronic case report forms will be used for this study with patients completing the study questionnaires confidentially on electronic tablets, and these data will be uploaded to a web-based server. Table 1 provides a summary of the data collection process and timing.

**Table 1 T1:** PROMISE study – summary of data collection

**Study procedure**	**Enrollment**	**Randomization**	**Screening test**	**Implant**	**1 month**^ **a** ^	**3 months**^ **b** ^	**6 months**^ **b** ^	**9 months**^ **b** ^	**12 months**^ **b** ^	**18 months**^ **b** ^	**24 months**^ **b** ^	**Unscheduled**	**Early discontinue**^ **c** ^
Time window (days)	-90 to 0	0	0 to 57	3 to 60	10 to 67	68 to 137	138 to 228	229 to 319	320 to 455	456 to 637	638 to 789	NA	NA
Informed consent	**X**												
Demographics (age, gender)	**X**												
Medical history	**X**												
Inclusion/exclusion criteria	**X**	**X**											
Pain location	**X**	**X**											
Pain diary (complete prior to visit)		**X**			**X**	**X**	**X**	**X**	**X**	**X**	**X**		**X**
OMM treatment plan		**X**			**X**	**X**	**X**	**X**	**X**	**X**	**X**		
Questionnaires (ODI, SF-36, EQ-5D^d^, Pittsburgh Sleep Quality Index, employment status, pain and/or paresthesia map)		**X**				**X**	**X**	**X**	**X**	**X**	**X**		**X**
Randomization assignment		**X**											
Neuropathic pain (DN4)		**X**											
PGIC, Patient satisfaction with therapy						**X**	**X**	**X**	**X**	**X**	**X**		**X**
Nondrug pain treatment and other healthcare use assessment		**X**	**X**	**X**	**X**	**X**	**X**	**X**	**X**	**X**	**X**		**X**
Payer information (US only)	**X**								**X**		**X**		
Medication assessment		**X**	**X**	**X**	**X**	**X**	**X**	**X**	**X**	**X**	**X**		**X**
Event assessment^d^		**X**	**X**	**X**	**X**	**X**	**X**	**X**	**X**	**X**	**X**	**X**	**X**

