Screening test assessment			**X**										
Implant information			**X**	**X**									
Request for change in randomized therapy							**X**	**X**	**X**	**X**	**X**	**X**^ **e** ^	
SCS therapy thresholds							**X**						
Device interrogation (initial and final)				**X**^ **f** ^	**X**	**X**	**X**	**X**	**X**	**X**	**X**	**X**	**X**

DN4, Douleur neuropathique en 4 questions; ODI, Oswestry Disability Index; OMM, optimal medical management; PGIC, Patient Global Impression of Change; SF-36, Short-Form 36; SCS, spinal cord stimulation.

^a^For subjects randomized to SCS, the 1-month visit should occur a minimum of 7 days after implant (or screening test if the test was unsuccessful).

^**b**^Visits should occur within the window but at least 2 weeks after the previous visit.

^c^Early discontinuation, collect data if possible.

^d^When possible, collect additional EuroQoL (EQ-5D) at time of event if device-related event requiring surgical intervention or hospitalization occurred.

^e^Only after 6 months.

^f^No initial interrogation at implant, final only.

#### **
*Primary outcome*
**

The primary outcome is the proportion of subjects with ≥50% reduction in low back pain intensity measured using the NPRS at 6 months [18]. Pain relief will be assessed as a reduction of the 11-point NPRS. Patients will record their low back and leg pain using a (paper) pain diary two times per day, once in the morning and once in the evening, for a 7-day period within 2 weeks prior to the randomization visit and subsequent scheduled study visits. For the initial baseline pain diary, patients are required to complete at least 5 of 7 days in their entirety, or they will not proceed to randomization. The proportion of subjects in each group with ≥50% reduction in average low back pain score at the end of Period I compared with baseline will be calculated.

#### **
*Secondary outcomes*
**

Secondary outcomes are: Back and leg NPRS score [18]; Oswestry Disability Index version 2 [19]; and Physical Component Summary score on the Short-Form 36 [20].

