Other outcomes include: Mental Component Summary score on Short-Form 36 [20]; EuroQoL 5D-5 L (EQ-5D-5 L) [22]; Pittsburgh Sleep Quality Index [23]; healthcare use related to the pain condition and to its treatment (for example, managing adverse events, interventions, investigations, drugs, length and number of inpatient hospitalizations, and number of emergency room, office, and other healthcare-related visits) [24]; employment status ('What is your current employment status?’ , 'If out of work: what is the main reason you are out of work?’); patient satisfaction ('Would you recommend this therapy to patients suffering from pain similar to yours?’ , 'Overall how satisfied or unsatisfied are you with this therapy?’); Patient Global Impression of Change version 2 [25]; programming parameters and paresthesia coverage; and adverse events (adverse events and device deficiencies documentation will include date of adverse event or device deficiency, diagnosis and description of the event, assessment of seriousness of the event, treatment of the event, outcome or resolution and date of the event, and relationship of the event to the device or to OMM – in addition to the standard questionnaire data collection schedule, the EQ-5D-5 L will be collected, when possible, whenever a device-related adverse event occurs that might require a surgical intervention or hospitalization).

#### **
*Process measures*
**

At the screening and baseline visits, the following additional information will be collected: subject demographics (for example, age, gender) and a neuropathic pain assessment by clinician-administered diagnostic questionnaire (Douleur Neuropathique en 4 questions) to discriminate neuropathic pain components of low back pain [26]. Subjects who proceed to device implantation will have the following information collected: pain/paresthesia map, parameter settings, electrode location, and device implant information (that is, model, serial number). Patients receiving SCS therapy will have a device interrogation at each visit, and at only the 6-month visit data will be gathered on the parameters at which SCS paresthesia is perceived, is comfortable, and becomes uncomfortable. Unscheduled patient visits could occur between scheduled study follow-up visits due to patient discontinuation from the study or device reprogramming and management of any complications.

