Missing data are a potential source of bias. A rigorous study design and execution will help prevent the incidence of missing data from occurring. For the primary objective, patients with missing data at the end of Period I will be treated as nonresponders (failures). With this approach, we assume that nonresponders in both treatment groups have no change in their outcomes compared with baseline. This method has been chosen over more complex imputation methods, such as multiple imputation, because it has been empirically demonstrated in trials of chronic pain to produce conservative treatment effects [28]. For the secondary study objectives, no change from baseline will be assumed for patients with missing data. For completers’ and as-treated supporting analyses, only completers will be included in the analysis.

Period II is the long-term follow-up phase, which includes the possibility for patients to change from their original treatment assignment to the alternative treatment. The objectives of Period II are to compare within-patient changes (that is, baseline versus follow-up) in each group. Because the study design allows patients to change from the randomized treatment group to the alternative treatment after 6 months of follow-up, the analysis of objectives in Period II will be based on the treatment patients actually received and not on the randomization assignment. Only completers will be included.

Unadjusted *P* values will be reported. To maintain an overall type I error rate at 0.05, a fixed-sequence method for the multiplicity adjustment of hierarchical endpoints will be used to test the primary and secondary objectives. No multiplicity adjustment will be performed for evaluations of the additional study objectives. A validated statistical software package will be used for the analyses of the study results (for example, SAS, SPLUS). These analyses are detailed in a statistical analysis plan.

#### **
*Economic evaluation*
**

Economic analyses consider the costs and effectiveness of treatments. Costs will be calculated by multiplying units of healthcare use used by the cost of each unit. Effectiveness will be expressed as quality-adjusted life-years, with these data derived from patients’ responses to the EQ-5D-5 L.

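### The event-triggered EQ-5D-5L is limited to device-related events, so in Period I an event-time utility can be recorded only in the SCS arm (minor)

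*Protocol article*

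**What the plan says.** In the protocol article's Assessments section, the list of other outcomes says that, "in addition to the standard questionnaire data collection schedule", the EQ-5D-5L will be collected when possible "whenever a device-related adverse event occurs that might require a surgical intervention or hospitalization". Table 1, footnote d, states the rule again: "When possible, collect additional EuroQoL (EQ-5D) at time of event if device-related event requiring surgical intervention or hospitalization occurred". Both restrict the extra reading to device-related events. They differ on severity: the text includes events that may turn out to need surgery or admission, the footnote only those that do need it.

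Other parts of the article bear on this:

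- **Scheduled EQ-5D.** The Table 1 row "Questionnaires (ODI, SF-36, EQ-5D^d^, Pittsburgh Sleep Quality Index, employment status, pain and/or paresthesia map" is marked at randomization, at 3, 6, 9, 12, 18 and 24 months, and at early discontinuation. It is not marked at 1 month. The schedule does not differ by arm.
- **Event attribution.** The adverse event record includes the "relationship of the event to the device or to OMM".
- **Allocation.** Under Design and setting, "Patients will be randomized 1:1 to SCS using the Specify® 5-6-5 surgical lead (Medtronic, Inc.) plus OMM (SCS group) or to OMM alone". Patients may change treatment only after the 6-month assessment.
- **Economic evaluation.** "Effectiveness will be expressed as quality-adjusted life-years", derived from the EQ-5D-5L. QALYs are reported for the two groups at 6, 12 and 24 months, and a cost-utility model extends to 15 years. The methods are deferred to a health economic analysis plan.

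**The concern.** The condition that triggers the extra reading is tied to treatment. An OMM patient has no study device in Period I and so cannot have a device-related event. If that patient is admitted for a drug or injection complication and recovers before the next visit, no utility reading reflects it. An SCS patient admitted for a device complication can have one taken at the low point. The adverse event record already foresees events related to OMM, so the omission is not for want of a category.

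What is at stake is the cost-effectiveness objective. If event readings are put into the QALY curve, or are the only source of event decrements in the model, part of the difference between groups reflects when utility was measured. A later analysis plan can leave the SCS event readings out, but it cannot recover OMM readings that were never taken.

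**Working it through.** The article gives no figure for this rule, so there is none to reproduce. The check has two parts.

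**1. Who can get an event-time reading**

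| Event leading to surgery or hospitalization | SCS arm, Period I | OMM arm, Period I | After a switch from OMM to SCS |
|---|---|---|---|
| Device-related | Yes, when possible | Cannot occur | Yes, when possible |
| OMM-related | No | No | No |
| Other cause | No | No | No |

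The rule divides by type of event. Because device-related events are confined to one arm before month 6, it also divides by arm in Period I.

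**2. Possible size if event readings enter the QALY curve**

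Inputs from Table 1: scheduled EQ-5D readings are 3 months apart up to month 12 (L = 0.25 year) and 6 months apart after that (L = 0.5 year).

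Assumptions, none of them in the document:
- linear interpolation between readings;
- one event reading per affected patient, a utility d below the line joining the two flanking scheduled readings;
- recovery before the next visit;
- d between 0.1 and 0.4;
- a share e of SCS patients affected, between 5% and 20%.

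One extra point removes a triangle from the area under the curve:

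loss per event = 0.5 × L × d

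- 3-month gap: 0.5 × 0.25 × 0.1 = 0.0125, up to 0.5 × 0.25 × 0.4 = 0.05 QALY.
- 6-month gap: 0.5 × 0.5 × 0.1 = 0.025, up to 0.5 × 0.5 × 0.4 = 0.10 QALY.

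shift in the SCS mean = e × loss per event

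- 3-month gap: 0.05 × 0.0125 = 0.0006, up to 0.20 × 0.05 = 0.01 QALY.
- 6-month gap: 0.05 × 0.025 = 0.00125, up to 0.20 × 0.10 = 0.02 QALY.

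The overall range is therefore roughly 0.001 to 0.02 QALY. Within Period I, where the split by arm is complete, only the 3-month gaps apply and the ceiling is 0.01. For scale over the same six months, a sustained utility gain of 0.1 is worth 0.1 × 0.5 = 0.05 QALY.

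This shift is the difference between calculating with and without the event reading. It is not all error, because the patient did lose utility. For a dip of 0.2 the actual loss is 0.2 × 2/52 = 0.0077 if it lasts two weeks and 0.2 × 8/52 = 0.0308 if it lasts eight. The interpolated loss in a 3-month gap is 0.5 × 0.25 × 0.2 = 0.025 in both cases. One extra point can thus overstate or understate the loss. The same dip in an OMM patient that resolves between visits counts as zero.

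If event readings stay out of the base-case QALY, the shift is zero.

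**The case against.** The strongest reply is that the rule captures the harm that SCS adds. OMM is given in both arms, so OMM-related admissions can occur in either and trigger an extra reading in neither. Device complications belong to SCS, and a utility loss attached to them is at least partly a real treatment difference. This stands as far as it goes. It does not remove the asymmetry if OMM-related events differ in frequency between the arms, and the article gives no ground for assuming that they are equal.

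A reader might infer that utility losses in OMM patients are never measured. The document does not support that. OMM patients complete the same scheduled EQ-5D, which captures any loss still present at a visit, and those who switch after 6 months come under the device-related trigger.

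A reader might also infer that the QALY comparison is already biased. That does not follow either. QALYs could be computed from scheduled visits only, or the model could take other decrements from elsewhere. The article leaves this to the health economic analysis plan, and that deferral is not a fault.

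One might add that events reclassified later by the clinical events committee would lack a reading. The Trial committees section says that the committee reviews relationship to SCS therapy but not when, so the point cannot be pressed.

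Finally, cost-effectiveness is an additional objective, outside the fixed-sequence testing, and the extra reading is taken only when possible. Both points are correct and keep the matter minor.

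**Conclusion.** The point holds in limited form, as a minor one. The stated collection rule allows event-time utility to be recorded only in the SCS arm during Period I, and it gives OMM-related and other serious events no event-time reading in either arm. The two statements of the rule also define different sets of events.

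The consequence for the economic comparison is conditional. If the readings enter the QALY curve, or are the only event decrements in the model, the comparison is measured differentially, probably to the disadvantage of SCS. The 0.001 to 0.02 QALY range applies to the curve calculation and rests wholly on the assumed dips, event rates and linear interpolation; the effect on the model was not sized. The primary and secondary endpoints do not use these readings and are unaffected.

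**What to change.** Reword the sentence in the list of other outcomes and Table 1 footnote d so that they state one identical trigger: collect the additional EQ-5D-5L, when possible, at any adverse event requiring surgery or hospitalization, whatever its attributed cause and whichever treatment the patient is receiving. This makes the trigger neutral between arms, removes its dependence on a relatedness judgment and settles the difference in wording between the two places.

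The change is one sentence and one footnote. The cost is a short questionnaire at some additional hospitalizations, on tablets already used in the trial and still only when possible. It has to be made at collection, because readings not taken at the time of an event cannot be obtained afterwards. How the readings are then used remains a matter for the health economic analysis plan.

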### Sample size and power calculations

Based on the results of the PROCESS study [8], with the assumption that OMM will provide slightly better low back pain relief and a conservative estimate using intention-to-treat analysis, the sample size calculation assumed a 20% between-group difference in the responder rate, which is defined as patients achieving ≥50% low back pain relief, with a 40% response rate for the SCS group and 20% for OMM group. The sample size was calculated using EAST version 5.4, the module Binomial Superiority Trials: two-sample test – difference of proportions, with the following sample size parameters: control group proportion response = 0.2, difference in proportion = 0.2, significance level = 0.05 (two-sided), power = 90%, assigned fraction = 0.5 (randomization ratio = 1:1), unpooled standard deviation and continuity correction for the standardized test statistics; one unequally spaced interim look at 66% (2/3) of the sample for sample size re-estimation, and the Lan–DeMets with O’Brien–Fleming boundary to reject the null hypothesis. These resulted in a total required sample size of 212 randomized subjects (106 subjects per treatment group). To reduce the possibility that one site with atypical results will overly influence combined results, no site can randomize more than 25 of 212 subjects without prior approval. If the sample size is extended, no site can randomize more than 10% of the patients. Assuming 30% pre-randomization attrition, up to 300 subjects may be enrolled.

A single interim analysis is planned after 140 randomized subjects reach the end of Period I. This analysis will provide data to support a decision to re-estimate the sample size if necessary in order to achieve conditional statistical power of at least 90%. For planning and simulation purposes, a ceiling of 400 randomized patients is imposed for the final analysis.

Enrolment, randomization, and follow-up will continue during the interim analysis. The interim analysis will be conducted by an independent statistician, and one of the following possible outcomes will be communicated to the trial sponsor: continue the study with a total of 212 subjects (implies that ≥90% conditional power will be achieved with *n* = 212); or increase the sample size to a specified size in order to achieve ≥90% conditional power to achieve superiority based on the observed interim results.

If the sample size must be increased, the sponsor will determine whether or not to continue the study. It is not anticipated that the sample size will be reduced below 212.

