### Data analysis

#### **
*Statistical analysis*
**

For primary and secondary objectives, the primary analysis method will follow the intention-to-treat principle supported by completers’ and as-treated analyses. The following definitions will be applied: intention-to-treat analysis, between-group comparison based on random allocation of all subjects at the 6-month visit; completers’ analysis, between-group comparison based on random allocation of subjects with complete data at the 6-month visit; and as-treated analysis, between-group analysis based on the treatment subjects with complete data at the 6-month visit received at the 6-month visit.

The primary objective will be compared by *Z*-test using unpooled standard deviation with continuity correction, and a logistic regression model will be used for exploratory analysis. Secondary objectives will be assessed using linear regression models. To assess potential differences in treatment effect across sites, a treatment-by-site interaction term will be added to models. If the treatment-by-site interaction term approaches significance (defined as <0.10, as recommended by Fleiss [27]), the term will remain in the final model along with the term for site. In this case, the results for the objective will also be tabulated by site. Factors that might explain differences among sites will be explored.

There is no compelling evidence of patient-related (for example, age, sex) factors that predict the outcome of SCS; however, in order to identify baseline characteristics that might have predictive effects on outcomes, exploratory analysis with regression models may be conducted including baseline covariates. For the analysis of secondary objectives, baseline assessments for pain score and the Oswestry Disability Index will be included in the regression models as covariates.

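### The listed inputs give 212 patients only without the stated continuity correction; with the planned corrected test, 212 gives about 87% power, not 90%

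*Protocol article*

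**What the plan says.** The article's section on sample size and power calculations gives these inputs:

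- Response rates: "control group proportion response = 0.2, difference in proportion = 0.2", put in words as "with a 40% response rate for the SCS group and 20% for OMM group".
- Error rates: "significance level = 0.05 (two-sided") and 90% power.
- Allocation: "assigned fraction = 0.5 (randomization ratio = 1:1").
- Test statistic: "unpooled standard deviation and continuity correction for the standardized test statistics".
- Interim: "one unequally spaced interim look at 66% (2/3) of the sample for sample size re-estimation", with a Lan-DeMets O'Brien-Fleming-type boundary for rejecting the null.

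The result follows directly: "These resulted in a total required sample size of 212 randomized subjects (106 subjects per treatment group").

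The statistical analysis part of the data analysis section says the primary objective will be tested by a Z-test "using unpooled standard deviation with continuity correction". The correction is thus claimed for both the sizing and the analysis.

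**The concern.** A continuity correction subtracts a fixed amount from the observed difference before it is divided by its standard error. At about 100 patients per arm and a 20-point difference this is not negligible: it usually adds about 10 patients per arm. Yet 212 is what the textbook unpooled formula gives with no correction.

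If the correction did not enter the calculation but will be applied in the analysis, the stated power on the primary endpoint is too high. The interim decision depends on the same statistic. Staying at 212 is said to mean at least 90% conditional power, and that can be judged only once it is settled which statistic is used.

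**Working it through.** **Inputs** (all from the sample size section): p1 = 0.20, p2 = 0.40, d = 0.20; two-sided alpha 0.05 (z = 1.960); power 90% (z = 1.2816); 1:1 allocation; one look after 140 of 212 patients. The unpooled variance term is 0.2 × 0.8 + 0.4 × 0.6 = 0.16 + 0.24 = 0.40.

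**Step 1. Reproduce 212 without the correction.**

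n per arm = (1.960 + 1.2816)² × 0.40 / 0.20² = 10.507 × 10 = 105.07

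This rounds up to 106 per arm, 212 in total. With the look at 140/212 the Lan-DeMets boundaries are 2.523 and 1.992, and the inflation factor is 1.0114. The total becomes 2 × 105.07 × 1.0114 = 212.5. Both routes match the stated figure to within rounding.

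**Step 2. Repeat with the correction.** With n per arm the correction to the difference is 1/n, so n must satisfy

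(0.20 − 1/n) / √(0.40/n) = 1.960 + 1.2816 = 3.2415 (unrounded quantiles)

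The solution is n = 114.9 per arm: 229.7 in total, or 230 after rounding up. With the look the total is about 232 by the normal approximation. Simulating the two-stage binomial design gives 89.7% power at 116 per arm and just over 90% at 117, so 232 to 234 in total.

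**Step 3. Try other readings of the inputs.**

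| Variant, 90% power | Total before the look |
|---|---|
| Unpooled, no correction | 212 |
| Unpooled, half-size correction 1/(2n) | about 220 |
| Unpooled, full correction 1/n | 230 |
| Pooled, no correction | 218 |
| Pooled, full correction | 238 |
| Unpooled, full correction, one-sided 0.05 | 192 |
| Pooled, full correction, one-sided 0.05 | 196 |

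No variant with a correction gives 212.

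**Step 4. Power of the planned test at 106 per arm, 40% versus 20%.** The standard error is √(0.40/106) = 0.0614.

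- Without correction: 0.20/0.0614 = 3.256, and Φ(3.256 − 1.960) = 90.2%.
- With correction: (0.20 − 1/106)/0.0614 = 3.102, and Φ(3.102 − 1.960) = 87.3%.

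These normal approximations were checked by exact binomial enumeration (single test) and by simulation of the two-stage design (2,000,000 runs, look at 70 per arm):

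| Test at 106 per arm | Single test at 1.96, exact | With the look, simulated |
|---|---|---|
| Unpooled, corrected (as planned) | 87.1% | 86.5% |
| Unpooled, uncorrected | 89.9% | 89.5% |

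If the look raises the final critical value to 1.993 but early rejection is not used, exact power of the corrected test is 86.3%.

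**Step 5. Where the power goes.** By exact enumeration at 106 per arm, the two-sided size of the corrected test is 3.4% when both rates are 0.20 and 3.7% when both are 0.30. The test is conservative, and the lost power corresponds to alpha that is not used.

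**The case against.** **Sample size re-estimation.** The final N is not fixed at 212. After 140 patients it may be raised, to a ceiling of 400, to reach at least 90% conditional power. Under one assumed rule (increase up to 200 per arm whenever conditional power at the observed effect is below 90%), a simulation put overall power near 97%, with N raised in 37% of runs. So 13% is not the overall risk of failure if re-estimation is carried out in full. That part stands. It does not rescue the stated figure, because 90% at 212 is given as the result of the listed inputs before any increase. The rule behind the 97% is an assumption, and the article leaves it to the sponsor whether to continue when an increase is needed.

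**Size of the problem.** The gap is about 3 points of power, type I error is protected, and a conservative pre-specified test is legitimate. This is right, and it limits the weight of the point: what is wrong is the power statement, not the choice of test.

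**Unknown cause.** The software output is not shown, so why the correction left no trace in 212 cannot be determined. That it was left out is inferred from the match in step 1. The disagreement between inputs and result does not depend on the cause.

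**Correction meant only for the analysis.** The article lists the correction among the sizing parameters. Even if it applied only to the analysis, the planned test would still have about 87% power at 212.

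**Conclusion.** The point holds. With the inputs as listed, 90% power needs about 230 patients in a fixed design and 232 to 234 with the interim look. The stated 212 is the uncorrected result. With the planned primary test, 212 patients give 86.5% to 87.1% power, so the type II error is about 13% against the stated 10%.

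This assumes true rates of 40% and 20%, the usual full correction of 1/n, and a final analysis at 212 with no increase at the interim. A half-size correction would soften it (exact power 88.5% as a single test) but would still not give 212.

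**What to change.** Settle one of the following in the protocol and the analysis plan before any unblinded interim result is available.

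1. **Keep the corrected test and correct the statement (least intrusive).** Say that 212 was obtained without the continuity correction and that the planned corrected Z-test has about 87% power at 106 per arm. Confirm that the conditional power calculation at the interim uses the corrected statistic. This costs one sentence, no patients and a slightly less favourable power figure.

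2. **Change the primary test to the pooled (score) Z-test without correction.** At 106 per arm its exact power is 89.6% as a single test and about 89% with the look. Its exact size is 5.0% with both rates at 0.20, though it rises to about 5.3% near 0.09. This also needs no patients, but it replaces a pre-specified test in an open-label trial, so the timing and reason must be documented. Dropping the correction while keeping the unpooled variance is less attractive: size is then 5.3% at 0.20.

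If the sponsor wants both the corrected test and a full 90% before re-estimation, the starting sample size would have to be 232 to 234 instead of 212, about 20 more patients.
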